# Improving difficult peripheral intravenous access requires thought, training and technology (DART^3^): a stepped-wedge, cluster randomised controlled trial protocol

**DOI:** 10.1186/s12913-023-09499-0

**Published:** 2023-06-07

**Keywords:** Ultrasonography, Interventional, Catheterisation, Peripheral, Vascular access devices, Randomised controlled trial, Implementation science

## Abstract

**Background:**

Peripheral intravenous catheters (PIVCs) are the most used invasive medical device in healthcare. Yet around half of insertion attempts are unsuccessful leading to delayed medical treatments and patient discomfort of harm. Ultrasound-guided PIVC (USGPIVC) insertion is an evidence-based intervention shown to improve insertion success especially in patients with Difficult IntraVenous Access (BMC Health Serv Res 22:220, 2022), however the implementation in some healthcare settings remains suboptimal. This study aims to co-design interventions that optimise ultrasound guided PIVC insertion in patients with DIVA, implement and evaluate these initiatives and develop scale up activities.

**Methods:**

A stepped-wedge cluster randomized controlled trial will be conducted in three hospitals (two adult, one paediatric) in Queensland, Australia. The intervention will be rolled out across 12 distinct clusters (four per hospital). Intervention development will be guided by Michie’s Behavior Change Wheel with the aim to increase local staff capability, opportunity, and motivation for appropriate, sustainable adoption of USGPIVC insertion. Eligible clusters include all wards or departments where > 10 PIVCs/week are typically inserted. All clusters will commence in the control (baseline) phase, then, one cluster per hospital will step up every two months, as feasible, to the implementation phase, where the intervention will be rolled out. Implementation strategies are tailored for each hospital by local investigators and advisory groups, through context assessments, staff surveys, and stakeholder interviews and informed by extensive consumer interviews and consultation. Outcome measures align with the RE-AIM framework including clinical-effectiveness outcomes (e.g., first-time PIVC insertion success for DIVA patients [primary outcome], number of insertion attempts); implementation outcomes (e.g., intervention fidelity, readiness assessment) and cost effectiveness outcomes. The Consolidated Framework for Implementation Research framework will be used to report the intervention as it was implemented; how people participated in and responded to the intervention; contextual influences and how the theory underpinning the intervention was realised and delivered at each site. A sustainability assessment will be undertaken at three- and six-months post intervention.

**Discussion:**

Study findings will help define systematic solutions to implement DIVA identification and escalation tools aiming to address consumer dissatisfaction with current PIVC insertion practices. Such actionable knowledge is critical for implementation of scale-up activities.

**Trial registration:**

Prospectively registered (Australian and New Zealand Clinical Trials Registry; ACTRN12621001497897).

**Supplementary Information:**

The online version contains supplementary material available at 10.1186/s12913-023-09499-0.

## Background

Peripheral intravenous catheters (PIVCs) are the most common invasive medical device [2], but can be difficult to insert. Up to 67% of first insertion attempts are unsuccessful, and 10–45% of patients require upwards of three insertion attempts [3, 4]. Multiple PIVC insertions are painful and an unnecessary burden on the health system through increased clinical workloads and cost [5]. One in three patients presenting to an emergency department, and one in two hospitalised patients present with Difficult IntraVenous Access (DIVA), making this a global issue that impacts millions annually [3, 6, 7]. This rate is likely to increase in coming years with growing chronic disease and morbidity burden in the community [8]. DIVA has various definitions [1, 9] but generally includes few or limited visible and/or palpable suitable veins, since these are the main criteria traditionally used to guide insertion using the “landmark” technique [10, 11].

Landmark PIVC insertion technique is typically used for PIVC insertion. However, the technique has limitations. It does not allow for the comprehensive assessment of vein caliber, depth, valve location, or tortuosity before device insertion, further tip position within vessel is unable to be confirmed (rather than the tissue) post-procedure [12]. An alternative to landmark insertion is ultrasound-guided (USG) insertion. This approach is well established for central venous catheters insertion but used less frequently for PIVC insertions [13]. Ultrasound provides the opportunity for thorough pre-assessment of the vein and enables visualisation of the needle and cannula throughout the entire PIVC insertion procedure [11, 12]. Over the past decade portable ultrasound machines have become increasingly available for use in practice - with excellent resolution for viewing peripheral veins [14]. Compared to landmark technique, USG insertions require fewer insertion attempts, less insertion time, and increase patient satisfaction [12, 15]. With a recent systematic review (8 studies; *n* = 1660 patients) confirmed overall superiority for USG insertion over landmark technique for PIVC insertion success (regardless of DIVA status; 81% vs. 70% respectively; odds ratio [OR] 2.49, 95% CI 1.37–4.52 [12]).

Currently, the choice of insertion technique (landmark or USG) by individual practitioners is inherently influenced by inserter experience and whether ultrasound training and equipment is available. The assessment of a patient’s DIVA status is inconsistently performed in practice [16]. To date, there is minimal evidence on the clinical impact of DIVA identification tools or escalation pathways (to more skilled inserters with USG skills) on patient outcomes [9, 16]. Consumers who have experienced DIVA report PIVC insertion practices vary widely across healthcare institutions influencing their experience and satisfaction with care [16, 17]. For patients who experience DIVA, ample evidence exists to support ultrasound-guided insertion as a first approach, rather than a rescue tool following failed landmark insertions [6, 18–20]. There is no known adverse effect of using ultrasound for PIVC insertion, and as such ultrasound-guided insertion is recommended for patients who experience in DIVA in international practice guidelines and clinical standards [21–23]. Despite its recognised efficacy and value, the implementation of ultrasound-guided PVC insertion is limited in many healthcare institutions, and current workforce and systems require purposeful adaptation [2, 9, 24]. This limitation is largely due to the requirement of additional equipment and processes, staff training and skills assessment. To achieve substantial patient and system benefit, prospective identification and escalation of patients with DIVA is required [3].

## Methods / design

### Study aims

The overall aim of the Difficult Access Requires Thought, Training and Technology (DART^3^) study is to implement and evaluate effective DIVA identification and escalation pathways to support PIVC insertion in adults and children, including appropriate use of ultrasound-guided procedures. The specific objectives of the study include the following:

To develop hospital-based interventions that support DIVA identification and escalation, adapted to the local health care context.To implement co-designed DIVA identification and escalation pathways, and evaluate their clinical effectiveness, cost effectiveness and implementation strategies.Develop recommendations for future strategic options for scale-up and optimised implementation of DIVA identification and escalation pathways in different settings.

### Hypotheses

The primary hypothesis is that implementation of tailored, co-designed DIVA identification and escalation pathways will significantly increase the incidence of first attempt PIVC insertion success for patients identified as having DIVA (primary outcome).

#### Secondary hypotheses

That implementation of the DIVA identification and escalation pathways:

H_2_ Will significantly increase the incidence of first attempt PIVC insertion success for **all patients**.

H_3_ Increases the proportion of patients with DIVA who have ultrasound used at first, or any attempt.

H_4_ Reduces the number of PIVC insertion attempts.

H_5_ Results in higher rates of successful PIVC placement and shorter time-to-therapy.

H_6_ Results in higher rates of alternate device or route use.

H_7_ Reduces post-insertion PIVC failure and complications.

H_8_ Results in increased PIVC dwell time.

H_9_ Is sustainable (i.e. There is no significant reduction in first time insertion success at 3 or 6 months compared to full implementation (month 10).

H_10_ Reduces rates of unnecessary PIVCs.

H^11^ Is cost-effective in Queensland healthcare settings.

H^12^ Reduces rates of cluster level routinely collected rates of primary BSI and S. Aureus BSI.

H^13^ Improves patient/carer and staff satisfaction with insertion procedure.

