### Sample size

Approximately 40% of studied patients are expected to be DIVA patients (8 per cluster step), and 60% non-DIVA (12 per cluster step). For DIVA patients, we assume baseline first attempt insertion success of 50% (based on meta-analysis [12] and our unpublished data on file) and anticipate a 50% relative improvement to 75% first insertion success [12]. We assume baseline first insertion success in non-DIVA patients of 70%, rising to 80% post- intervention. This is equivalent to an overall change for all patients from 62 to 78% first attempt insertion success. With 240 patients at each of the five data collection periods (baseline plus four steps), there will be > 90% power to detect a significant difference between the usual care and implementation phases (alpha = 0.05). See Supplementary Material 3: statistical analysis plan.

To measure sustainability of the effect of the implementation on the primary endpoint, we will additionally assess 240 patients at each sustainability time point (3 and 6 months). This leads to a total sample size of 1680 observations, consisting of 240 observations at each of the 7 periods (baseline, steps 1–4, 3- and 6-month follow-up).

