***Secondary***		
First attempt insertion success for all patients (regardless of DIVA status)	One needle puncture, by one inserter, to achieve successful of a functional (can be aspirated/flushed) PIVC ^2^	Hospital-based assessments
Number of attempts	Number of skin punctures to attempt PIVC insertion ^3^	Hospital-based assessments
Procedure outcome:	Successful PIVC insertion; time from PIVC referral to PIVC insertion (censored at 48 h); alternate device; alternate route (e.g., oral) ^4^	Hospital-based assessments
PIVC failure	Composite measure of local infection, primary bloodstream infection (BSI), occlusion, infiltration/extravasation, dislodgement (includes leaking), thrombosis and/or phlebitis ^6 7^	Hospital-based assessments
Insertion/post-insertion complications	Bruising, haematoma, nerve injury, arterial puncture, or skin injury as well as the individual components of PIVC failure (above) ^6 8^	Hospital-based assessments
PIVC dwell time	Time from PIVC insertion to PIVC removal (in hours) ^6^	Hospital-based assessments
PIVC necessity	PIVC used for fluids or medications within 24 h (excluding patients who require a prophylactic PIVC in situ as part of their treatment e.g., status epilepticus) ^5^	Hospital-based assessments
Incidence of blood stream infection	Cluster level routinely-collected rates of primary BSI and S. Aureus BSI ^9^	Hospital-based assessments
Economic outcomes		
Cost-effectiveness	Direct and indirect healthcare costs to the health system, patients/carers: (time to insertion/therapy, cost of products, number of staff, staff time, costs of responding to failed insertion including cancelled appointments)	Hospital-based assessments
Implementation outcome- reach		
Number of healthcare professionals attending Ultrasound training	Counts of clinicians attending ultrasound training	Hospital-based assessments
Number of staff accredited in ultrasound insertion	Per local ultrasound accreditation requirements	Hospital-based assessments
Implementation outcome—adoption		
Healthcare provider engagement	Proportion of patients assessed using the DIVA vein assessment tool	Hospital-based assessments
Ultrasound adoption	proportion of DIVA patients with ultrasound used at the first, or any attempt	Hospital-based assessments
Patient/carer/parent satisfaction and pain with insertion procedure	0–10 numeric rating scale ^6^	Hospital-based assessments

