### Evaluation of DART^3^ primary and secondary intervention outcomes (Effectiveness evaluation)

#### Statistical methods

Patient variables, staff and consumer satisfaction ratings, will be summarised using descriptive statistics. Mean and standard deviation will be used for normally distributed data, and median and interquartile range for data not normally distributed. Counts and percentages will be used to summarise categorical data. The between-group comparison of the primary outcome will be analysed using a mixed-effects logistic regression model. Fixed effects included in the model will be study phase (pre/post implementation) and step. Cluster will be included as a random effect to account for probable non-independence of observations within clusters. The individual will be the unit of analysis. Continuous secondary outcomes will be compared with mixed-effects linear regression, time-to-event secondary outcomes by multilevel survival modelling, and count outcomes by mixed-effects Poisson regression. All models will account for clustering. The primary analysis will be ‘intention-to- treat’, with ‘per protocol’ analyses assessing the effect of protocol compliance. A statistical analysis plan is outlined in Supplementary material 3.

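### H5 claims shorter time to therapy, but the outcome measured is time to PIVC insertion, in which patients treated by an alternate device or route have no event

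*Protocol article*

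**What the plan says.** Among the secondary hypotheses of the protocol article, H5 reads "Results in higher rates of successful PIVC placement and shorter time-to-therapy" and H6 reads "Results in higher rates of alternate device or route use".

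Table 1 holds the matching effectiveness outcomes in one row, the procedure outcome. Besides successful insertion, that row lists "time from PIVC referral to PIVC insertion (censored at 48 h); alternate device; alternate route (e.g., oral"). Alternate device and alternate route are thus outcomes in their own right, not forms of PIVC insertion.

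Therapy timing appears in one other place, inside the cost-effectiveness row, as one of several resource items: "time to insertion/therapy, cost of products, number of staff, staff time". It is not defined there as an effectiveness outcome.

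The Statistical methods section plans to analyse "time-to-event secondary outcomes by multilevel survival modelling". It states no rule for a patient who is treated without a PIVC.

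**The concern.** The hypothesis and the outcome name different events. H5 is about when treatment starts. The outcome records when a PIVC goes in. The two agree only for patients who receive a PIVC, and even then the interval from insertion to first dose is not captured.

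The mismatch would matter little if the affected patients were equally common before and after implementation, though it would still dilute a true effect. H6 predicts that they will not be. If more implementation-phase patients go to another device or to oral therapy, more of them lack an event in the H5 analysis, although some may have been treated promptly. A conclusion that the pathway did or did not shorten time to therapy would then rest on a quantity that does not measure it, and that can move against the intervention for a reason unrelated to delay.

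**Working it through.** **1. The plan's own figures.** The article gives no effect size, power or sample size for this outcome. Its one power statement, "there will be > 90% power to detect a significant difference between the usual care and implementation phases (alpha = 0.05"), concerns first-attempt success. It reproduces:
- Overall success: 0.4 × 0.50 + 0.6 × 0.70 = 0.62 and 0.4 × 0.75 + 0.6 × 0.80 = 0.78, as stated.
- Power uses the Hussey–Hughes stepped-wedge variance with 12 clusters, 5 periods and two-sided alpha 0.05 (sidedness assumed). For DIVA patients (8 per cluster-period) at ICC 0, the variance is 12 × (0.625 × 0.375 / 8) / 90 = 0.0039, so the standard error is 0.0625. Power is Φ(0.25 / 0.0625 − 1.96) = Φ(2.04) = 97.9%. The article states no ICC. Over an assumed range of 0 to 0.20, power is 93.3% to 97.9% for DIVA patients and 94.7% to 99.0% for all patients (20 per cluster-period).

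None of this depends on H5.

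**2. Who has an event.** By the written definition:

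| Patient | Therapy possible? | Event in the H5 outcome? |
|---|---|---|
| PIVC inserted within 48 h | yes | yes |
| Alternate device or route, no PIVC | yes | no |
| Neither | not by these means | no |

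The share without an event at 48 h is (alternate + neither). The first group may be on treatment and the second is not, but the outcome does not separate them.

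**3. Direction and possible size if alternate access displaces PIVCs.** All inputs here are assumptions, because the article gives no rate of alternate use and no distribution of waiting times. Time to therapy is exponential with median 2 h, every patient is treated, and a share a0 (usual care) or a1 (implementation) is treated by an alternate means with the same time distribution. Everyone else receives a PIVC, so each extra alternate patient is one PIVC fewer. A one-covariate Cox model was fitted to 200,000 simulated patients per phase, ignoring clustering and step. It shows bias, not precision. A hazard ratio above 1 favours the intervention.

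| a0 to a1 | True HR | Held to 48 h | Censored at switch |
|---|---|---|---|
| 5% to 5% | 1.00 | 1.00 | 1.00 |
| 2% to 5% | 1.00 | 0.89 | 0.97 |
| 5% to 10% | 1.00 | 0.86 | 0.95 |
| 5% to 15% | 1.00 | 0.75 | 0.89 |
| 10% to 20% | 1.00 | 0.77 | 0.89 |
| 5% to 5% | 1.20 | 1.13 | 1.20 |
| 5% to 10% | 1.20 | 0.96 | 1.14 |

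The last column can be checked by hand. Censoring at the switch leaves a hazard of insertion of (1 − a) times the hazard of therapy, so the ratio is true HR × (1 − a1)/(1 − a0). For 5% to 10% this is 0.90/0.95 = 0.95, and with a true HR of 1.20 it is 1.20 × 0.90/0.95 = 1.14.

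**4. The case without displacement.** Suppose (assumed) that PIVC / alternate / neither moves from 90% / 5% / 5% to 92% / 8% / 0%. Patients without a PIVC fall from 5 + 5 = 10% to 8 + 0 = 8%, so the measured outcome improves by 2 points. Patients with any access rise from 95% to 100%, a gain of 5 points. Here the outcome has the right sign and understates the benefit.

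**The case against.** **Unseen documents.** The procedure-outcome row carries a footnote whose text is not shown, and the analysis plan is supplementary material 3. Either may say that switched patients are censored at the switch or treated as a competing event. That is ordinary analysis-plan content and its absence from an article is no fault. This stands: holding switched patients to 48 h is the literal reading of the table, not an established rule. It changes the size of the distortion. No censoring rule, however, turns time to insertion into time to therapy.

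**Placement may rise too.** A reader might infer that better escalation will lengthen the measured time, so that H5 will point the wrong way. The documents do not support that as a general statement. The first half of H5 predicts more successful PIVC placement, and both placement and alternate use can grow by drawing on patients who previously received neither, as step 4 shows. Reversal needs displacement.

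**A figure in hours.** A reader might multiply an extra 10 points of alternate use by 48 − 4 = 44 h (alternate therapy assumed to start at 4 h) and report 4.4 h of spurious delay. The plan names no restricted mean, and neither the 10 points nor the 4 h has a source in the article.

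**Dwell time.** A reader might extend the criticism to H8. H8 predicts longer dwell, and Table 1 measures "Time from PIVC insertion to PIVC removal (in hours"), so hypothesis and outcome agree. PIVC failure and PIVC necessity are already separate outcomes. Preferring time to failure would be a matter of taste.

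**Importance.** This is half of one of twelve secondary hypotheses, and alternate device and route appear in the same table row, so a shift would be visible to an attentive reader. That limits the harm but does not make the H5 claim testable.

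**Conclusion.** The point holds for H5. As written, its time-to-therapy claim has no effectiveness outcome behind it, and the nearest outcome omits the patients that H6 expects to become more common. This much rests on the article's text alone.

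The bias runs against the intervention only to the extent that alternate access displaces PIVC insertion. Under full displacement and the assumed rises in alternate use, a true hazard ratio of 1.00 appears as 0.75 to 0.89 if switched patients are held to 48 h, and as 0.89 to 0.97 if they are censored at the switch. These are illustrations and not estimates, since the real rate of alternate use is unknown. Without displacement the outcome may be merely conservative. The primary outcome and its power are not touched.

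**What to change.** Restate the second half of H5 as time from referral to PIVC insertion, and keep the conclusion to that.

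Analyse it with alternate device or route as a competing event, showing the cumulative incidence of PIVC insertion and of alternate access side by side by phase. Both curves are needed. The insertion curve alone, or a subdistribution hazard model alone, keeps switched patients in the risk set and so repeats the held-to-48-h reading. Where the time of the switch was not recorded, report the shares with PIVC, alternate access and neither at 48 h.

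Where the time of alternate access or of therapy start is already recorded, also report time to first functional access or therapy by any device or route. The cost-effectiveness item suggests that some of this timing may exist.

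The cost is some added analysis and a narrower H5 claim. The type of alternate access is already an outcome, so the restated analysis needs no new variable. A new time stamp should not be counted on: the article, published on 7 June 2023, reports recruitment under way with completion expected around 31 July 2023, and timing not captured at baseline cannot be assumed recoverable. The change should be dated and made before the outcome data are compared by phase.

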### Setting and sampling

DART^3^ is a multi-site study involving three large tertiary hospitals in South-East Queensland, Australia. All hospitals (two adult and one paediatric) are government-funded, university affiliated teaching facilities.

Each hospital has four participating clusters (wards or departments), for a total of 12 clusters. Each cluster begins with a baseline phase, followed by a step up to the implementation phase, where the intervention is introduced, the study is completed by a sustainability phase, divided into three- and six-month time points. The total study timeframe will be 16-months and consist of seven steps. Hospital and cluster characteristics are outlined in Supplementary material 1. Eligible clusters include emergency departments, inpatient wards or critical care units (CCU, ICU) where greater than 10 PIVCs per week are typically inserted. Operating services, which theatres, radiology, rehabilitation, or psychiatric units, were not eligible for inclusion. All hospitalised patients (DIVA or non-DIVA) of any age prescribed a PIVC insertion (standard or long length PIVC) may be included. Patients requiring time-critical intravenous access (e.g., Medical Emergency calls, intraosseous access) will not be included in the study.

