Inserter (initial and/or successful inserter) satisfaction with escalation pathway	0–10 numeric rating scale ^6^	Hospital-based assessments
Attitude of healthcare providers with DIVA tools	Degree of acceptability of the DIVA tools by clinicians	Key stakeholder interviews
Implementation outcome - implementation		
Fidelity	Degree that the DIVA tools are implemented as planned in original protocol	Key stakeholder interviews
Feasibility	Extent that the DIVA tools can be carried out in specific settings	Key stakeholder interviews
Outer context	Macro-level external factors including social, funding, and leadership	Key stakeholder interviews
Inner context	Micro-level internal factors including behaviours, feedback.	Key stakeholder interviews
Implementation outcome—maintenance		
Sustainability of the intervention and effectiveness	First time insertion success at 3- or 6-month sustainability assessments	Hospital-based assessments
Satisfactory of stakeholders	0–10 numeric rating scale ^6^	Key stakeholder interviews
Financial sustainability	Explored in the cost-effectiveness analysis and qualitatively through interviews with executive stakeholders.	Key stakeholder interviews
Institutionalisation of interventions	Concerned with sustaining social behavioural change	Key stakeholder interviews

*RE-AIM* Reach, effectiveness, adoption, implementation, maintenance

Data collection will be facilitated using a custom-built REDCap (Research Electronic Data CAPture http://project-redcap.org/ Vanderbilt, USA) database. Research nurses will directly enter de-identified study data (data variables and time points outlined in Table 2 and supplementary material 5) in the clinical areas using study tablets with the REDCap application configured for this trial.

**Table 2 Tab2:** Data collection time points for DART^3^

Activities	Pre-implementation	SWRCT - implementation						
		Step 1	Step 2	Step 3	Step 4	Step 5	Step 6	Step 7
Establish site-specific advisory groups	**√**							
Qualitative interviews and evidence synthesis	**√**							
Economic interviews for PIVC insertion procedures	**√**	**√**	**√**	**√**	**√**	**√**		
Co-develop DIVA tool and escalation pathway	**√**							
Pilot-test and evaluate DIVA tool and escalation pathway prototypes for reliability, acceptability and reproducibility	**√**	**√**						
Implementation of site-specific DIVA tools across the 3 hospitals, 12 clusters in a staggered manner			**√**	**√**	**√**	**√**		

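### H9 defines sustainability as no significant fall from month 10, which tests whether a success rate is stable and not whether an effect has been kept

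*Protocol article*

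**What the plan says.** Under Secondary hypotheses, the protocol article spells out in H9 what sustainable means: "There is no significant reduction in first time insertion success at 3 or 6 months compared to full implementation (month 10"). The only inputs are success rates at month 10 and at the two later time points. Table 2 shows the fourth and last cluster of each hospital in implementation by step 5, so all of these rates come from after full roll-out.

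The Sample size section gives the purpose as "To measure sustainability of the effect of the implementation on the primary endpoint", and for this "we will additionally assess 240 patients at each sustainability time point (3 and 6 months"). The maintenance rows of Table 1 list the outcome as "First time insertion success at 3- or 6-month sustainability assessments", with no comparator.

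Nowhere does the article make H9 depend on the primary hypothesis, compare the later rates with usual care, or state how large a loss would count against sustainability.

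**The concern.** The stated aim is to see whether an effect lasts. An effect is a difference from usual care, and H9 contains no such difference. If the pathways change nothing, first-attempt success stays at its usual-care level, nothing falls, and H9 is met.

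The criterion also treats a non-significant result as support. With the planned numbers, a real and sizeable loss can go undetected and be read as sustained.

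What is at stake is the wording of one maintenance finding. The report could call the programme sustainable beside a null or inconclusive primary result, or after a substantial part of the gain has gone.

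**Working it through.** **Inputs from the article.**
- Clusters: 12 (Setting and sampling).
- Patients: 240 per period, and "Approximately 40% of studied patients are expected to be DIVA patients (8 per cluster step), and 60% non-DIVA (12 per cluster step"). That gives 12 × 8 = 96 DIVA patients per period.
- DIVA first-attempt success: 50% rising to 75%, a gain of 25 points.
- All patients: 62% rising to 78%, a gain of 16 points.
- Alpha: 0.05.

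**Assumptions.** The article does not state sidedness or an intracluster correlation (ICC). The test is taken as two-sided, with a fall as the failing direction. The ICC is varied. Month 10 is taken as the last step, with the same number of patients as the other periods. There is no secular trend.

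**The plan's own figures first.** 0.4 × 50% + 0.6 × 70% = 62%; 0.4 × 75% + 0.6 × 80% = 78%; 7 × 240 = 1,680. Power of the stepped-wedge comparison was computed with 5 periods, 3 clusters per step, fixed period effects and a random cluster effect. For DIVA patients it is 97.9% at ICC 0, 92.7% at 0.05 and 90.7% at 0.10. For all patients it is 99.0%, 93.6% and 92.5%. The stated power above 90% reproduces.

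**H9 at one time point.** With n per period and true rates p₀ (month 10) and p₁ (later):

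P(no significant fall) ≈ Φ(1.96 − (p₀ − p₁)/SE), where SE = √[p₀(1−p₀)/n + p₁(1−p₁)/n].

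DIVA patients, n = 96:
- No effect (50% throughout) or full gain kept (75% throughout): the difference is 0, so Φ(1.96) = 97.5% in both cases.
- 60% of the gain kept: 50 + 0.6 × 25 = 65%. SE = √(0.1875/96 + 0.2275/96) = 0.0657; 0.10/0.0657 = 1.52; Φ(0.44) = 67%.
- Half kept: 62.5%. SE = √(0.1875/96 + 0.2344/96) = 0.0663; 0.125/0.0663 = 1.89; Φ(0.07) = 53%.

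**H9 at both time points.** The two comparisons share the month-10 sample, so they were simulated (pooled two-proportion tests, independent observations):

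| True state | DIVA (n = 96) | All patients (n = 240) |
|---|---|---|
| No effect | 95.4% | 95.4% |
| Full gain kept | 95.5% | 95.5% |
| 60% of gain kept | 52% | 48% |
| Half of gain kept | 36% | 32% |

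With cluster effects at ICC 0.02 to 0.05, the no-effect figure is 95.4 to 96.0% and the 60%-kept figure is 47 to 54%. For half kept, a cluster-stratified simulation in DIVA patients at ICC 0.05 gave 35%.

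**Other readings.** If one time point without a fall were enough, the figures are 99.5% with no effect and 82% (DIVA) or 79% (all) with 60% kept. With a one-sided 0.05 test at both time points, they are about 91% with no effect and 38% or 34% with 60% kept.

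**With a condition on the primary result.** If H9 is claimed only when the effect test also favours the programme (ICC 0 to 0.05), a no-effect programme is called sustainable in about 2 to 2.5% of trials. One keeping its full gain is called sustainable in 90 to 95%. One keeping 60% still passes in about 50% (DIVA) or 45 to 47% (all). The condition removes the first problem but not the second.

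**The case against.** The strongest reply is that 95% is no discovery about this trial. Any test at this level finds no fall about that often when nothing falls. That is correct, and it is why a programme with no effect and a fully sustained one score alike. The point is that equality, not the number itself.

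A reader might infer that H9 perversely ranks an ineffective programme above an effective one that keeps 60% of its gain. The documents do not support reading it that way. Keeping 60% means a real 10-point fall, which a test for reduction ought to flag, and the gap between 95% and about half reflects the power of that test. A reader might also infer that H9 decides the maintenance conclusion and the scale-up advice. It does not: Table 1 lists further maintenance outcomes, and the article says that the process evaluation informs scale-up.

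It is also fair that the aim in the Sample size section presupposes an effect, that a null primary result would be reported beside H9, and that the separate statistical analysis plan, not shown here, may add a condition. These points limit the consequence. They do not change the published definition, which the article states in full and which contains neither an effect nor a tolerable loss.

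**Conclusion.** The point stands as a modest fault in one secondary hypothesis. It does not touch the primary analysis or the trial's main conclusion.

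H9 as worded cannot separate a sustained benefit from no benefit, since each meets it in about 95% of trials at both time points. Because it relies on non-significance, it is also met about half the time after a loss of 40% of the planned gain and about 35% of the time after a loss of half.

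The exact figures rest on a two-sided 0.05 test, equal numbers per period, no secular trend and the assumed ICC. Across the other readings checked, the no-effect figure runs from about 91% to 99.5%. The equality between no effect and full retention needs none of these choices beyond a stable rate.

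**What to change.** Reword H9 in three respects.
- Draw a sustainability conclusion only if the primary analysis shows a benefit.
- Base it on the estimated change in first-attempt success from month 10 to 3 months and to 6 months, each with a confidence interval and read against the size of the primary effect, instead of on non-significance alone.
- If the primary hypothesis is not met, report the 3- and 6-month rates descriptively and draw no sustainability conclusion.

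Any comparison with the usual-care rate should be descriptive and labelled non-concurrent, because no cluster remains in usual care by then.

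The cost is a short change of wording in H9 and the matching analysis text, with no extra patients or data. There are two downsides. H9 can no longer be claimed if the primary hypothesis fails. The interval may also be too wide to support a claim: for DIVA patients stable at 75%, ignoring clustering, its half-width is 1.96 × √(2 × 0.75 × 0.25/96) = 1.96 × 0.0625 = 12 points, about half of the planned 25-point gain.
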